#### Statistical Methods for All Quantitative Outcomes

We will describe the characteristics of the caregivers and children using the mean (SD) and median (IQR) for continuous data (based on data distribution) and proportions for categorical data, at each time of measurement. To evaluate changes in key outcomes over time (baseline and 6 months), we will analyze the prospective cohort survey data using logistic and linear regression models for binary and continuous outcomes, respectively, specified in Table 3. Binary outcomes will be reported as odds ratios (as change in proportions) with 95% CIs; continuous outcomes will be reported as mean differences (as change in means) with 95% CIs. We will conduct a generalized estimating equation approach to account for repeated measures (ie, baseline and 6 months) for each participant. We will undertake stratified analyses by service site to explore whether outcomes vary by site. In consideration of the change in participants’ characteristics between baseline and 6-month surveys due to loss to follow-up, we will control for family socioeconomic characteristics. Missing data will be handled using appropriate statistical techniques (such as multiple imputation for missing at random). We will describe the proportions of measures derived from data analytics from eHub users (specified in Table 3). We will conduct all analyses using STATA (version 16) or SAS (SAS Institute) statistical software packages.

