### Objectives

This protocol details the methods to evaluate the primary and secondary outcomes of the eHub for caregivers with children aged 0-12 years, with a specific focus on populations with low education, diverse languages, and socioeconomic deprivation. We will undertake a type 3 implementation impact evaluation as defined by Curran et al [1]. Type 3 implementation impact evaluation tests an implementation strategy while observing and gathering information on the intervention’s impact on relevant outcomes. In this protocol, implementation will be assessed as a primary outcome using Proctor’s outcomes for the implementation framework [20]. Secondary outcomes will include family information and service access and use, as well as child and caregiver mental health.

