**Demographics**			
	Postcode, single or couple parent, country of birth, language spoken at home, education status, number of adversities	Prospective cohort survey (baseline): The population cohort—eHub metadata will provide demographic characteristics of caregivers who access the eHub, including postcode to link SEIFA and parents’ place of birth compared with caregiver data from ABS.	

^a^eHub: Child and Family eHub.

^b^SEIFA: Socio-Economic Index for Area.

^c^IRSD: Index of Relative Socio-Economic Disadvantage.

^d^ABS: Australian Bureau of Statistics.

**Table 4 table4:** Secondary evaluation outcomes and associated measures.

Secondary outcomes: impact		Measure

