### Statistical Analysis

#### Sample Size Estimation for Impact Evaluation

We will recruit a total of 270 caregivers to give the study 90% power to detect an 11% increase in the proportion of caregivers accessing services via the eHub, that is, from 9% to 20% based on previous research [34], with a hypothetical 5% increase without the intervention. This allows for a 10% loss to follow-up.

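### Equity of cohort outcomes is promised, but variation in change is examined only by separate site fits and priority-group variables are used only for adjustment

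*Protocol article*

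**What the plan says.** In the protocol article, Statistical Methods for All Quantitative Outcomes plans logistic and linear models of change from baseline to 6 months, with GEE for the repeated measures and 95% CIs throughout. On variation in outcome it says: "We will undertake stratified analyses by service site to explore whether outcomes vary by site". On socioeconomic variables it says that "we will control for family socioeconomic characteristics", and the reason given is that loss to follow-up may change the make-up of the sample between surveys.

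The Objectives describe an evaluation "with a specific focus on populations with low education, diverse languages, and socioeconomic deprivation". Digital Solutions (Introduction) hypothesises that better access will make child mental health outcomes more equitable. The Discussion promises evidence on whether the eHub serves priority populations and reduces inequity in access and uptake.

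The variables needed are in hand. The demographics rows of Table 3 list, for the baseline cohort survey: "Postcode, single or couple parent, country of birth, language spoken at home, education status, number of adversities".

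**The concern.** Adjusting for a variable removes its influence from the overall estimate. It does not show whether change differs across that variable's levels. As written, the cohort analysis will give an average change, and a change per site, but no estimate of whether caregivers with less education, another home language or more adversity changed as much as the rest. That is the comparison the equity hypothesis needs.

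The site analysis has a related gap. Its stated purpose is to see whether outcomes vary by site, but three separate fits yield three changes and no contrast between them. A reader is left to compare the three by eye, and the easiest comparison, which sites reached significance, is unreliable at these sizes.

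Site results cannot fill the equity gap either. Site Selection notes disadvantaged areas inside otherwise advantaged Marrickville. In Table 1, Wyndham Vale and Fairfield have nearly the same year 12 completion (48.8% and 48.2%) but differ in SEIFA quintile (second and first) and in the share born overseas (40.1% and 56%). A real site difference could not be assigned to education, language or deprivation.

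**Working it through.** **Inputs from Sample Size Estimation for Impact Evaluation.** "We will recruit a total of 270 caregivers to give the study 90% power"; the change is "that is, from 9% to 20% based on previous research"; loss to follow-up is 10%, so 270 × 0.9 = 243 completers.

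**Assumptions, not in the document.** Two-sided 5% level (in line with the 95% CIs); equal recruitment by site, so 243 / 3 = 81 completers each; the within-person correlation of the binary outcome, or equivalently the share of caregivers who switch from access to no access.

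**The plan's own figure.** For 9% v 20% at 90% power, two independent proportions need 214 per group (238 after 10% loss), or 232 (258) with continuity correction. A paired (McNemar) calculation gives 127 (142) with 2% switching off and 248 (276) with the maximum 9%. None gives exactly 270, and the role of the "with a hypothetical 5% increase without the intervention" is not stated; both are separate matters. For this point it is enough that 243 completers give about 93% power unpaired and 89-99% paired for the pooled change. The stated power is for that pooled change and not for any stratum.

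**Discordance.** With p1 = 0.09 and p2 = 0.20, d = p1(1 - p2) + p2(1 - p1) - 2φ√[p1(1 - p1)p2(1 - p2)] = 0.254 - 2φ(0.1145). This gives 0.254, 0.185 and 0.140 at φ = 0, 0.3 and 0.5.

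**Precision per site.** SE = √[(d - 0.11²)/81], with 0.11² = 0.0121. At φ = 0, √(0.2419/81) = 0.0546.

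**Power per site.** Φ{[0.11√81 - 1.96√d] / √(d - 0.0121)}. At φ = 0, (0.990 - 0.988)/0.492 is about 0, so power is 50%.

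**Chance of mixed significance** among three sites with the same true change: 1 - q³ - (1 - q)³, where q is the power per site.

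| φ | d | 95% half-width per site (points) | Power per site | Mixed significance | Half-width, difference of two sites (× √2) |
|---|---|---|---|---|---|
| 0 | 0.254 | 10.7 | 50% | 75% | 15.1 |
| 0.3 | 0.185 | 9.1 | 64% | 69% | 12.8 |
| 0.5 | 0.140 | 7.8 | 76% | 54% | 11.0 |

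Parameterised instead by 2% to 9% of caregivers switching off (d = 0.15 to 0.29), power per site is 73% down to 45%, and mixed significance occurs in 59-75% of studies. Together: power 45-76%, mixed results 54-75%.

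**What an interaction could show.** For two groups of 122 and 121, the SE of the difference in change is √[(d - 0.0121)(1/122 + 1/121)].
- d = 0.15: SE = 0.0476. The difference detectable with 80% power is 2.80 × 0.0476 = 13 points.
- d = 0.254: SE = 0.0631. The detectable difference is 18 points.
- Power for an 11-point difference in change is 64% and 41% respectively.
- With a one-third/two-thirds split (81 and 162), the figures become 14-19 points and 59% down to 38%.

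**The case against.** Four points on the other side carry weight.

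- **Equity is not ignored.** A reader might infer that the equity question is wholly untested. It is not. Coverage, a primary outcome in Table 3, compares vulnerable families reached, by postcode-linked SEIFA and country of birth, with census-type denominators, and maps visits to each tier against demographics. But it concerns reach and use and is described only. It does not use education or home language, and it rests on analytics that the Recruitment section calls unidentifiable, with no stated link to cohort outcomes. The gap is therefore confined to equity of cohort outcomes.
- **The plan does not compare sites by p-value.** A reader might infer that chance site differences will be reported as real. The text calls the site analysis exploratory and reports CIs, so the 54-75% applies only if the strata are read by significance. A reader could also difference the independent site estimates by hand. The plan names no such contrast, however, and for priority groups there are no strata to difference.
- **Interaction terms may sit in a statistical analysis plan that is not shown.** That is fair, so the point does not rest on missing detail. It rests on the article's named methods not matching the question it sets for site or its own equity hypothesis.
- **The remedy is weak.** Interactions will be imprecise, and in a cohort without a control group a time-by-education term mixes any eHub effect with secular trend and regression to the mean. Both objections stand and limit what may be claimed.

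It is also tempting to fault the lack of a stated site main effect in the pooled model. This has little consequence: site is constant within a caregiver, and with complete pairs in a linear model it leaves the estimated change unaltered.

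**Conclusion.** The concern holds in a limited form. The article promises evidence on equitable outcomes, collects the variables, and then names no analysis of whether change in the cohort outcomes differs by priority group. Its only look at variation, separate fits by site, does not estimate the between-site difference it is meant to explore. With about 81 completers per site, power per site for the planned 11-point rise is about 45-76%, and reading the strata by significance would show disagreement in about 54-75% of studies with identical true change.

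These figures assume equal sites, a two-sided 5% level, and φ of 0 to 0.5 or 2-9% switching off. They concern one binary outcome; the continuous outcomes, such as K10, were not examined. The documents do not support saying that equity is untested altogether, that spurious site differences will be reported, or that the proposed terms would show who benefited from the eHub.

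**What to change.** In the pooled GEE:

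1. Replace or supplement the stratified fits with a time × site interaction. Give one joint test, and take the site-specific changes and their 95% CIs from that model.
2. Add, one at a time, time × education, time × language spoken at home, and time × number of adversities (or SEIFA). Report the difference in change with its 95% CI. For binary outcomes, give it in percentage points as well as on the odds-ratio scale.
3. Label all of these exploratory and estimation-focused. Four interactions per outcome would, if independent, give at least one nominally significant result in 1 - 0.95⁴ = 19% of cases with no true difference, so no claim should rest on a single p-value. The Results section says analysis took place from February to May 2025; terms added after that should be called post hoc.
4. State that they describe differential change over six months, not differential effect of the eHub, and word the Discussion's promise about priority populations to match.

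The cost is a few model terms on data already collected. The downside is imprecision, which must be stated: about ±11-15 points for a difference between two sites, and 80% power only for differences in change of about 13-18 points with an even split.

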#### Qualitative Data Analysis: Caregiver and Intersectoral Service Provider Interviews

Experienced research assistants at each site will use deductive and inductive analysis of stakeholder interviews using framework analysis. Framework analysis is suitable for this applied study because the technique is not aligned with any specific epistemological stance and places the research questions at the forefront of the analysis [35]. Interviews will be transcribed, and NVivo (version 14; Lumivero) will be used to code data from interviews. The first 10% of interviews at each site will be double-coded by research assistants, and any issues will be resolved prior to finalizing coding for all interview participants.

#### Health Economic Analysis

Using study protocols and budgets, the cost of implementing the eHub model will be estimated. This will include fixed or upfront costs of building the eHub as well as variable ongoing costs of maintaining and staffing. The cost of caregiver-reported intersectoral service use will be estimated. Cost effectiveness will be calculated as a cost per additional child or caregiver engaged with the program and a cost per additional child with unmet needs who accesses the eHub model. The cost of a national roll-out of the eHub model will be estimated based on the number of children serviced by the study versus the whole Australian population of children. An estimation will be made on the number of eHub local modifications needed nationally.

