**Cost**			
	Cost of providing the eHub, intersectoral service use, and effectiveness of eHub	Prospective cohort survey (6 months): Costs of implementation and national scaling of the model will be estimated (using study protocols, budgets, and population of children). The costs associated with caregiver-reported intersectoral service use will be estimated. Cost-effectiveness estimated based on the number of families engaged and those with unmet needs being met.	

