**Child mental health**		
	Child mental health needs met: Did the caregivers’ child have unmet mental health care needs? If yes, were they met by the eHub resources?	Prospective cohort survey (baseline and 6 months): Unmet child mental health need [30]
	Child mental health symptoms: Is eHub exposure associated with improvements in parent-reported child mental health symptoms?	Prospective cohort survey Child aged 2 months to 2 years—Survey (baseline and 6 months) of Well-Being of Young Children [31] Child aged 2-12 years—Strengths and Difficulties Questionnaire [32]

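### The Health Economic Analysis counts access by children with unmet needs where Table 3 counts unmet needs being met, so that ratio is a cost per user reached, not a cost per outcome

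*Protocol article*

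**What the plan says.** Cost is one of the implementation outcomes in Table 3, the table of primary outcomes. Its cost row reads: "Cost-effectiveness estimated based on the number of families engaged and those with unmet needs being met". That names two effect units, engagement and needs met.

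The Health Economic Analysis section also gives two ratios. The first: "Cost effectiveness will be calculated as a cost per additional child or caregiver engaged with the program". The second is "a cost per additional child with unmet needs who accesses the eHub model".

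On the cost side, implementation cost is split: "This will include fixed or upfront costs of building the eHub as well as variable ongoing costs of maintaining and staffing". Service use is costed as well: "The cost of caregiver-reported intersectoral service use will be estimated". The section does not say whether service-use cost enters either ratio.

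Table 4, under child mental health, asks: "Did the caregivers’ child have unmet mental health care needs? If yes, were they met by the eHub resources". Its measure of unmet child mental health need is in the cohort survey at baseline and 6 months. The section on baseline data collection places the baseline survey at the consenting caregiver's first access to the eHub.

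The cost of a national roll-out is to be "estimated based on the number of children serviced by the study versus the whole Australian population of children", and the number of local modifications needed nationally is to be estimated too.

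**The concern.** Both definitions stand in the current text and both claim to be the cost-effectiveness measure. An analyst following Table 3 would count needs met. An analyst following the Health Economic Analysis would count children who had a need and arrived at the platform. The second count contains no outcome, because what happens to the child after arrival does not enter it.

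The article describes the eHub as potentially cost-effective and scalable, and plans to present results to state and federal government contacts. A cost per user reached that carries the name cost-effectiveness could be read there as evidence of value for money in meeting children's needs, which it cannot show.

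**Working it through.** The article states no cost-effectiveness figure, so there is nothing to reproduce. The check is a comparison of the two texts, then a short piece of algebra.

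**Step 1: the units side by side.**

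| | Table 3, cost row | Health Economic Analysis |
|---|---|---|
| First ratio | families engaged | child or caregiver engaged |
| Second ratio | unmet needs being met | child with unmet needs who accesses the eHub |

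The first row broadly agrees. The counting unit differs (families against child or caregiver), but the inclusion criteria allow only one caregiver per family, so in the cohort caregivers and families coincide. The second row does not agree: one entry is an outcome, the other an exposure.

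**Step 2: can the access count respond to the outcome?** Among the data sources the article lists, unmet child mental health need is measured only in the cohort survey. The analytics on all users cover usage, satisfaction and brief demographics. The second ratio therefore has to be built from the cohort. There, baseline data are taken at first access, so a child with unmet need at baseline has met the access condition before follow-up begins. Recruitment also runs through a QR code to REDCap, so some enrolled caregivers may hardly use the platform afterwards. Even if such caregivers were left out, the count would depend on use and not on needs met.

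**Step 3: the algebra.** Let C be the cost in the numerator, A the number of children with unmet need who access the eHub, and m the share of them whose need is met at 6 months.

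- Access ratio (Health Economic Analysis): C / A
- Needs-met ratio (Table 3): C / (A × m) = (C / A) / m

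m does not appear in the access ratio. The documents give none of C, A or m. For illustration only, assume C = 100,000 currency units and A = 100:

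| m (assumed) | Access ratio | Needs-met ratio |
|---|---|---|
| 0% | 1,000 | undefined (no needs met) |
| 10% | 1,000 | 100,000 / 10 = 10,000 |
| 25% | 1,000 | 100,000 / 25 = 4,000 |
| 50% | 1,000 | 100,000 / 50 = 2,000 |
| 100% | 1,000 | 100,000 / 100 = 1,000 |

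The two agree only if every need is met. Otherwise the access ratio is the lower. The table shows the structure of the problem and is not an estimate of its size in this study.

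**Step 4: are the data for Table 3's unit available?** Yes. Table 4 collects unmet child mental health need at baseline and 6 months. Reading Table 3's unmet needs as this measure is an inference, but it is the only measure of unmet need listed among the outcomes.

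**The case against.** The strongest reply is that this is a type 3 hybrid study with implementation as its primary outcome, and cost sits in the implementation table. Cost per user engaged or reached is a legitimate measure of implementation efficiency. That stands, and it is a reason to keep those ratios. It does not justify naming the access ratio as cost-effectiveness when Table 3 specifies needs met. Nor is this detail that an article leaves to a fuller document, because both definitions are stated and they differ.

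A reader might infer that the ratio is the same whether or not the eHub works in any sense. That goes too far. It is insensitive to needs met, but it responds to reach, and could respond to service-use costs if these enter the numerator.

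A reader might also object that *additional* has no meaning without a control group. For access to or engagement with a new platform it can be read against no eHub, where there are no users. The difficulty is real only for needs met, because some needs would have been resolved anyway. The one counterfactual in the article, a hypothetical 5% increase in the sample size section, concerns service access and not unmet need. The preferred unit therefore carries its own limitation and must be presented accordingly.

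Finally, the roll-out sentence might be taken to mean that the build cost is multiplied up to the national population, or that every child is reached. The text does not establish either. It separates fixed from variable costs and estimates local modifications separately, which fits poorly with purely proportional scaling, and nothing in it bars the use of observed reach. No overstatement of national cost can be calculated from the documents.

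**Conclusion.** The concern holds for one of the two ratios. Table 3 and the Health Economic Analysis give different second effect units, and the version in the Health Economic Analysis is a cost per child reached. It is invariant to the share of needs met. That follows from the definitions and from baseline being taken at first access, and needs no assumed figure. The size of the discrepancy depends wholly on the share of needs met, which the documents do not give.

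The engagement ratio is consistent enough with Table 3 to stand. The roll-out wording calls only for clarification: it gives no age limit, although the eHub is for children aged 0-12 years, and it does not say what reach is assumed.

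This should be corrected before the economic results are reported. It does not affect data collection or the other outcome analyses.

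**What to change.** 1. In the Health Economic Analysis, replace the second ratio with cost per child with unmet mental health need at baseline whose need is met at 6 months, in line with Table 3 and the Table 4 measure. State whether service-use cost is in the numerator.
2. Report it as a before-after figure without *additional*, and say that the single-arm design has no counterfactual for needs met.
3. Keep the engagement and access ratios, labelled as cost per user engaged and cost per user reached.
4. As a minor clarification, state that the roll-out base is children aged 0-12 years and which reach is assumed.

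The cost is some rewording and one more line in the costing sheet, with no new data. The article dates analysis to February to May 2025 and dissemination to 2026. If the ratios have already been calculated, the needs-met ratio can be added and the access ratio relabelled. The downside is that the cost per outcome will look less favourable than the cost per child reached unless every need is met.

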### Ethical Considerations

This study received ethics approval from the Royal Children’s Hospital Human Research Ethics Committee (HREC #84970). All participants will provide informed consent prior to enrollment. Caregivers will access study information and consent materials via a secure online platform (REDCap) and will have the opportunity to ask questions before providing electronic consent. Participation is voluntary, and individuals may withdraw at any time without consequence. All data collected during the study will be deidentified prior to analysis. Participant information will be stored on secure servers in accordance with institutional data security protocols to protect privacy and confidentiality. Only approved members of the research team will have access to identifiable information, which will be stored separately from deidentified datasets. Participants will be reimbursed with a US $20 gift voucher for their time and contribution to the study.

